# A community-based pragmatic, controlled trial for preventing and reducing oral diseases among 1–6-year-old children visiting Anganwadi centers, under the Integrated Child Development Scheme, India

**DOI:** 10.1186/s12889-019-7874-y

**Published:** 2019-12-03

**Keywords:** Caregivers, Child, Community health workers, Dental caries, Health education, Dental, Streptococcus mutans

## Abstract

**Background:**

Early childhood caries (ECC) has reached epidemic proportions affecting millions of children worldwide. Its prevention becomes imperative owing to the significant morbidity and financial implications involved with its treatment. The Integrated Child Development Scheme (ICDS), launched in India to provide mid-day meals, pre-school education and primary healthcare to children, can be utilised to counsel and deliver oral health education to mothers. The purpose of the study is to compare the effect of an oral health care package (OHCP) with usual care on the change in dental disease status among 1 to 3-year-old children at Anganwadi centres (AWC) in periurban areas of Chandigarh and rural areas of Cuttack, Orissa over a follow-up period of three years.

**Methods:**

Two geographically distant ICDS blocks would be selected at each of the two study sites and would be randomly allocated to intervention and control group. Closely located AWCs under each of the selected blocks shall constitute the study setting. OHCP would be delivered to the mothers of the 1–6-year-old children enrolled in the AWCs of the experimental group whereas mothers under control group would receive usual care advice available at the AWCs.

**Discussion:**

ECC prevention had conventionally focused upon testing effectiveness of programs targeting behaviour change among the caregivers and children, but surprisingly minimal efforts have been made to seek translation of these efforts into reduction of ECC at the community level. The present study has two components; testing effect of altering maternal and child behavioral aspects on ECC incidence through cohort follow up of 1–3-year-old children for three consecutive years and cross-sectional follow up of all available 1–6-year old children at the selected AWCs at regular intervals to look for change in prevalence of ECC at community level. In other regions of the world surveys of ECC prevalence before and after the intensive educational programs have shown a significant reduction in ECC prevalence. A similar decline can be anticipated through this program.

**Trial registration:**

This trial has been prospectively registered at Clinical Trials Registry, India (CTRI/2019/02/017556, 08 February 2019).

## Background

Early childhood caries (ECC) is a significant public health challenge that has reached epidemic proportions and has affected millions of young children both in developed and developing nations [1–3]. While considering the potential burden and the morbidity associated with this disease, several policies have been formed and implemented at the international level to decrease the overall burden of the disease across various age groups by setting age-specific targets. A joint group of the World Health Organization (WHO) and the Federation Dentaire Internationale (FDI) proposed the global average for dental caries to be 3 DMFT for 12-year-olds and 50% of 5–6-year-olds to be free of dental caries by 2000 [4]. Prevalence of dental caries is on a decline in many industrialised nations due to their well-structured oral health programs, and a good percentage of their GDP had been directed towards oral health, and the majority of them have achieved these goals. However, the developing nations like India are far from reaching WHO targets due to lack of any national-level policies for prevention and control of dental diseases. The problem is compounded by several factors including the disparity in the distribution of population, with two-thirds of the Indian community residing in rural areas, of which 40% are children [5]. The dramatic improvement in the dentist-population ratio over the past 6–7 decades from 1:301,000 in the 1960s to an average of 1:9992 in 2016 has not equally reflected in the rural and urban areas with the majority being concentrated in the latter (1:4000) and only about 25–30% of them serving in the rural regions (1:30,000); consequentially even necessary oral health facilities are not available in some of the areas [6]. The prevalence of ECC in Indian children less than 5 years ranges between 50 and 70%; the significant sequelae being root stumps warranting extractions and abscesses resulting from pulpal involvement of primary teeth, ultimately affecting the speech, mastication and esthetics of the child [7–11]. Literature regarding the impact of ECC on the quality of life of children as well as their families reports that despite comprehensive oral rehabilitation of the affected dentition, their quality of life remained significantly lower than that of children who did not develop the disease [12]. Keeping in mind the significant morbidity, loss of school hours in children and substantial finances involved in the treatment of ECC, the only practically viable solution for dealing with ECC is its prevention.

Prevention of ECC can be brought through education of expectant mothers and mothers of young children regarding appropriate oral hygiene measures and dietary practices. In a utopian universe, this task would best be carried out by trained dental professionals. However, the country faces a gross disparity in the regional distribution of the dental health workforce, as mentioned before. A promising alternative workforce for the task seems to be the female workers at the Anganwadi centres (AWC) under the ICDS scheme which was launched in 1975 to provide mid-day meal, pre-school education and primary healthcare to children under 6 years of age. These workers can be used to effectively counsel and deliver the oral health education to both children and mothers’ thus serving as the much-needed initiative at the national level. ICDS scheme is an ideal example of community participation under the Primary Health Care concept (Alma Ata declaration 1978). As of 2015, the number of operational AWCs in India is 1,349,091 with each centre covering a population of 1000 in rural and urban areas and 700 in Tribal regions [13]. Anganwadi workers (AWW) promote and monitor overall child development, carry out additional feeding, immunisation, dispense vitamin A, iron and folic acid tablets and referral to the medical care facility. AWWs also provide outreach services by visiting door-to-door in the community as agents of social change mobilisation for better care of young children, girls and women. Though adequately trained on issues concerning general health, various studies have cited limited oral health knowledge and awareness among them [14, 15]. Nevertheless, they appear to be a potential health workforce that is yet to be utilised for controlling and limiting many prevalent oral diseases like ECC in India.

A one-year pilot project funded by the Department of Science and Technology, Government of India (2014–15), was carried out to develop an oral health care package for prevention and control of oral diseases among mothers and pre-school children, and to test whether AWWs could be utilised for delivering this package.

The present research project aims to compare the effect of the above tested oral health care package versus routine dental care advice generally imparted by the AWWs on change in dental caries, gingival health and S mutans levels among 1 to 6-year-old children and KAP regarding oral health among their mothers at AWCs. The study shall be simultaneously carried out at two geographically distant sites; peri-urban areas of Chandigarh and rural parts of Cuttack, Orissa. In contrast to Chandigarh, rural Cuttack has got a significant proportion of the tribal population with differing socio-economic, cultural background and dietary habits etc. Keeping two sites in the study shall also additionally permit comparison of study outcomes between these two different populations [16, 17].

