## Methods

### Study design

This will be a pragmatic, two-arm, parallel-group, community-based controlled trial with clusters of AWCs within ICDS blocks as the unit of allocation. Two geographically distant ICDS blocks will be selected at each of the study sites, viz. Chandigarh and Cuttack. The selected blocks will be randomly allocated to the intervention and control group using sealed envelopes by a statistician who will not be the part of this study. AWCs under each of the two selected blocks shall be enumerated and, from them, one AWC will be randomly selected, and further AWCs located adjacent to this AWC will then be chosen so that a cluster of AWCs is formed within the block. This cluster of AWCs will constitute a unit of allocation. A typical cluster-randomised controlled trial should have a large number of small-sized clusters, randomly allocated to an intervention and control arm. However, for logistic reasons, we have opted for a pragmatic design in which only two large-sized clusters at each study centre (Chandigarh and Cuttack) would be compared.

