### Sample size estimation

Sample size calculation for the study has been based upon a similar study conducted by Lawrence HP et al., 2008 for prevention of dental caries among aboriginal children in Canada, with 2-year, follow up [18]. In the above study, the mean (SD) change of dmfs in intervention and control arm was 11 (14.3) and 13.47 (16.3), respectively, resulting in a mean difference of 2.47.

Assuming a 5% alpha error and 20% beta error, to detect a mean difference with standard deviations as above, using the sample size formula (z_1-α/2_ + z_1-β_)^2^ x (σ_1_^2^ + σ_2_^2^)/(μ_1_-μ_2_)^2^, the required sample size has been calculated to be approximately 605 in each arm. The design effect due to clustering has not been included, because we do not have prior information about the intra-class correlation within a cluster. To account for an attrition in the number of study subjects, and to account for a decrease in the effect size (due to a potential waning in the performance of AWWs in the intervention clusters over the three-year study period, and a possible Hawthorne effect) it was decided to inflate the sample size approximately 1.5 times, resulting in 950subjects in each arm at each study center (Chandigarh and Cuttack). On average, around 25 children are attached to each AWC. Therefore, at each study centre, a cluster of 40 AWCs will be selected within each of the two ICDS blocks, and the blocks will be randomly located to the intervention and the control arm.

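### With one allocated cluster per arm at each site, a comparison of Chandigarh with Cuttack can only be descriptive, and the Background should say so

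*Protocol article*

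**What the plan says.** The Background (protocol article) explains why two sites were chosen. Rural Cuttack has a substantial tribal population and differs from peri-urban Chandigarh in socio-economic status, culture and diet. It then adds: "Keeping two sites in the study shall also additionally permit comparison of study outcomes between these two different populations".

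Study design makes the cluster of AWCs within an ICDS block the unit of allocation. Two blocks are chosen per site and one goes to each arm. Each cluster is built from one randomly chosen AWC and its neighbours. The section acknowledges that a typical cluster trial would have many small clusters, and says that on logistical grounds "only two large-sized clusters at each study centre (Chandigarh and Cuttack) would be compared".

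Sample size estimation sizes the intervention-versus-control difference in dmfs change: "Assuming a 5% alpha error and 20% beta error", it finds that "the required sample size has been calculated to be approximately 605 in each arm". This is then inflated, "resulting in 950subjects in each arm at each study center (Chandigarh and Cuttack"). No design effect is applied.

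The Plan for analysis describes comparisons between the two arms. It states no hypothesis about a site difference in the intervention effect.

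**The concern.** The Background sentence states what the design makes possible, and nothing later in the article limits it. A reader would take it that if the package shows a different effect on dmfs in Chandigarh than in Cuttack, the difference can be attributed to the two populations. With one block in each site-by-arm cell, the same pattern could arise because four localities differ in water, diet, access to dentists, AWC staff or baseline caries. The data could not show which explanation is right.

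What is at stake is the interpretation of site-specific results. An apparent difference could be reported as the package working better in one population, and an apparent similarity as evidence that it works equally in both. Neither conclusion would have support at the level at which allocation took place. No analysis plan could repair this, because the replication is absent from the design.

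**Working it through.** **Inputs** (Sample size estimation and Study design). Change in dmfs: "intervention and control arm was 11 (14.3) and 13.47 (16.3), respectively", "resulting in a mean difference of 2.47". Two-sided alpha 5%, power 80%. Per arm per site: 605 before inflation, 950 after. Allocated clusters: two per site, four in all. Block-level intra-class correlation (ICC): not given.

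**1. The plan's own figure.** Sum of variances: 14.3² + 16.3² = 204.49 + 265.69 = 470.18. Then n = (1.96 + 0.8416)² × 470.18 / 2.47² = 604.9, so 605 per arm is reproduced. It applies to a single arm contrast.

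**2. Degrees of freedom between blocks.** There are four block means. The overall mean, arm, site and site-by-arm terms use all four: 4 − 4 = 0 remain. If the site-by-arm term is assumed to be zero, 4 − 3 = 1 remains. So the block-level error of a plain site difference can be estimated only by assuming that the effect does not differ by site.

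**3. What each contrast carries.** Let τ² be the variance between blocks and n the number of children per arm per site.

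- Site difference in effect: variance = 4τ² + 2 × 470.18 / n.
- Plain site difference, averaged over arms: variance = τ² + 470.18 / (2n).

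The second term in each shrinks as children are added. The τ² term does not, and with one block per cell τ² cannot be estimated alongside a site difference in effect.

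**4. Illustration with τ² = 0.** For a site difference in effect, SE = √(940.36 / n), which is 1.247 at n = 605 and 0.995 at n = 950. Power = Φ(difference / SE − 1.96).

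| Assumed site difference in effect (dmfs) | 605 per arm per site | 950 per arm per site |
|---|---|---|
| 1.235 (half the planned effect) | 16.6% | 23.6% |
| 2.47 (the whole planned effect) | 50.8% | 69.9% |
| 3.705 (1.5 times) | 84.4% | 96.1% |

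The documents give no value for this difference, so every row is an assumption. The 950 column also assumes no attrition. For a plain site difference of 2.47 in mean dmfs change, again with τ² = 0, power is 97.7% at 605 and 99.9% at 950. Numbers of children are not the limit there; the two blocks per site are.

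**5. Sensitivity to block variation (assumed ICCs).** For a site difference in effect of 2.47, SE² = (940.36 / n) × (1 + (n − 1) × ICC).

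| Block-level ICC | Power at 605 | Power at 950 |
|---|---|---|
| 0.001 | 34.6% | 42.8% |
| 0.005 | 16.6% | 17.8% |
| 0.01 | 11.3% | 11.6% |

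These figures treat the ICC as known, which this design cannot provide. At 0.01, going from 605 to 950 children changes almost nothing, as step 3 implies.

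**The case against.** The strongest defence is that the sentence claims little. It is one remark in the Background, presented as an extra benefit, and it speaks of comparing outcomes. It does not announce a test of whether the intervention effect differs by site. The 80% power is stated only for the arm contrast, and leaving an additional comparison unpowered is ordinary. Study design is open about having few clusters, and how site enters the analysis may be set out in a full protocol or analysis plan that is not shown.

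Much of this stands. A reader might infer that the protocol promises a powered test of a site difference in effect and that its power is at best 51–70%. The documents support neither half. No such test is promised, and 51–70% holds only for an assumed difference of 2.47 with clustering ignored; it is not a ceiling, since a difference of 3.705 would have 84–96%. A reader might also infer that a false site difference would drive the decision to scale up. The Discussion ties scaling up to whether the approach proves effective and practical, and does not mention a difference between sites.

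It could also be said that 40 AWCs per cluster supply replication. They allow variation among AWCs within a block to be estimated. They are neighbouring centres allocated together, so they say nothing about variation between blocks.

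The defence does not reach the structural point. Study design admits that clusters are few but attaches no limit to the Background sentence, and no unseen analysis plan can create a second block in a cell.

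**Conclusion.** The concern holds as a limit on interpretation, and it is minor. With one allocated cluster per site-by-arm cell, a site difference in the intervention effect is fully confounded with differences among four blocks and has no block-level error estimate. A plain site difference in outcome rests on two blocks per site. This conclusion follows from the stated allocation alone and needs no assumption about effect size or ICC.

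The power figures only illustrate it. About 51% at 605 and 70% at 950 per arm per site depend on an assumed site difference of 2.47 dmfs, no clustering and, for 950, no attrition. They do not show that a stated power claim is wrong, because the protocol makes none for this comparison.

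**What to change.** **Background.** Qualify the sentence on the two sites, for example: *Comparisons between the sites will be descriptive, as site-specific estimates with confidence intervals. With one block per arm at each site, the design does not support an inferential claim that the intervention effect differs between the two populations.* It would help to add that intervals built from variation among children or AWCs do not include variation between blocks.

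**Plan for analysis.** Where the arms are compared across both centres, include site as a stratum, because allocation was made within site. Note there that this contrast also rests on only two blocks per arm.

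No change to the sample size section is needed for this point.

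**Cost.** Wording in two sections, with no additional children, visits or clusters. The downside is that an inferential claim about a difference between the populations is given up.

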## Methods

### Study design

This will be a pragmatic, two-arm, parallel-group, community-based controlled trial with clusters of AWCs within ICDS blocks as the unit of allocation. Two geographically distant ICDS blocks will be selected at each of the study sites, viz. Chandigarh and Cuttack. The selected blocks will be randomly allocated to the intervention and control group using sealed envelopes by a statistician who will not be the part of this study. AWCs under each of the two selected blocks shall be enumerated and, from them, one AWC will be randomly selected, and further AWCs located adjacent to this AWC will then be chosen so that a cluster of AWCs is formed within the block. This cluster of AWCs will constitute a unit of allocation. A typical cluster-randomised controlled trial should have a large number of small-sized clusters, randomly allocated to an intervention and control arm. However, for logistic reasons, we have opted for a pragmatic design in which only two large-sized clusters at each study centre (Chandigarh and Cuttack) would be compared.

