### Plan of study (Fig. 1)

#### Measurement of variables

The following demographic variables and potential confounders will be recorded at enrollment; socio-economic status of children, number of siblings, order and age of children, child anthropometry (weight & BMI), eating patterns, oral health services utilisation by children and health behaviors of children, maternal and child medical history and health literacy levels of mothers etc.

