### Data monitoring, quality assurance and auditing

The real-time data entry would be done using a mobile tablet-based data collection platform. To ensure project efficiency we will have (a) well trained team of dentists and field workers (b) calibration of dentists and field workers before commencement of study, at 6 months, 1 year and 2 years (c) outcome assessors who will be blinded for all follow up examinations (d) geographical distance between the ICDS blocks to avoid contamination, (e) weekly meetings with the research staff, (f) logs of all study participant contacts. To ensure efficient and accurate data management, the electronic data collection system will centrally collect all the data on the server and have an administrative account to (i) maintain records of all the data gathered from the participants during each visit (ii) central data processing and (iii) fortnightly data checks. Security of the data will be maintained through regular backups, and all computers and specific data files will be password protected and kept in a locked file cabinet. Only the project Principal Investigator will have access to this administrative account.

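### At each site block is fully aliased with arm, yet beyond the rural or peri-urban setting the only stated rule for pairing blocks is distance, with none that they be alike on caries-related features

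*Protocol article*

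**What the plan says.** Study design sets the rule for choosing blocks: "Two geographically distant ICDS blocks will be selected at each of the study sites, viz. Chandigarh and Cuttack". The purpose of the distance is given under Data monitoring, quality assurance and auditing: "geographical distance between the ICDS blocks to avoid contamination". The abstract and Background also confine the setting to peri-urban Chandigarh and rural Cuttack.

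Allocation is random: "The selected blocks will be randomly allocated to the intervention and control group using sealed envelopes by a statistician". There is one block per arm at each site, and Study design is open about this: "only two large-sized clusters at each study centre (Chandigarh and Cuttack) would be compared". It calls the layout atypical for a cluster trial and gives logistic reasons. Within a block the sample is one locality, grown from a single randomly drawn AWC: "further AWCs located adjacent to this AWC will then be chosen so that a cluster of AWCs is formed within the block".

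Background, explaining why two sites are used, says of the second that "rural Cuttack has got a significant proportion of the tribal population with differing socio-economic, cultural background and dietary habits etc". Measurement of variables lists confounders to be recorded at enrolment, among them "socio-economic status of children, number of siblings, order and age of children, child anthropometry (weight & BMI), eating patterns". The list is left open-ended. Plan for analysis names Student's t-test or the Mann-Whitney test for quantitative outcomes, and a choice of repeated-measures models. It commits none of these to covariate adjustment.

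**The concern.** When each arm at a site is one block, randomisation decides which way a difference between the blocks points, but it cannot balance the two. Any caries-related difference between them (diet, socio-economic mix, local services) enters the dmfs contrast as if the package had caused it, in either direction. Using change in dmfs does not prevent this, because such factors act on the increment as well as on the starting level. Taking neighbouring AWCs adds to the exposure, since a local peculiarity is not averaged over the block.

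Once the number of blocks is fixed at two per site, choosing a similar pair is the main design-stage protection left. The plan states a pairing rule that serves contamination control and none that serves comparability. A later analysis plan cannot repair how the blocks were chosen.

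**Working it through.** **The plan's own figure.** Inputs from Sample size estimation: SDs 14.3 and 16.3, difference 2.47, two-sided 5% alpha, 80% power. (1.960 + 0.842)² × (14.3² + 16.3²) / 2.47² = 604.9, which agrees with the stated figure of about 605 per arm. The calculation is right for its inputs, and the point below does not depend on it.

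**Aliasing within a site.** With two blocks, an intercept, arm and any block-level covariate make three columns of rank 2. Arm and block cannot be separated at any number of children. With the sites pooled there are four blocks. Intercept, site and arm leave one residual degree of freedom. A block-level covariate uses it up, or is itself collinear with site and arm if the block gap is the same at both sites.

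**Chance difference between two unmatched blocks.** Planning variance = (14.3² + 16.3²)/2 = 235.1. The protocol says it has no information on the intra-class correlation (ICC), so values of 0.01 and 0.02 at block level are assumed.

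| Assumed ICC | Block SD = √(ICC × 235.1) | SD of difference = √2 × block SD | Same, half the block variance removed |
|---|---|---|---|
| 0.01 | 1.53 | 2.17 | 1.53 |
| 0.02 | 2.17 | 3.07 | 2.17 |

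Against 2.47, the unmatched SDs are 88% and 124% of the planned effect. With half the block variance removed by matching (also assumed), they are 62% and 88%.

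**Effect on the test.** With all 950 per arm at a site analysed, SE = √(470.18/950) = 0.70, so an observed difference of 1.96 × 0.7035 = 1.38 surfaces is significant. With 605 per arm after attrition, SE = 0.88 and the threshold is 1.73. If the package has no effect and the blocks differ by an assumed fixed amount, the unadjusted test rejects as follows.

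| Assumed block difference (surfaces) | 950 per arm | 605 per arm |
|---|---|---|
| 0.5 | 11% | 9% |
| 1.0 | 30% | 21% |
| 2.0 | 81% | 62% |

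**Tribal composition at Cuttack, as an example.** Shift = gap in tribal share between the blocks × gap in mean dmfs change between tribal and other children. Both inputs are assumed: 10 to 50 percentage points and 2 to 4 surfaces.

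- 0.1 × 2 = 0.2 surfaces, 8% of 2.47
- 0.3 × 3 = 0.9 surfaces, 36%
- 0.5 × 4 = 2.0 surfaces, 81%

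If the gap exists only at Cuttack and the sites are pooled with equal weight, these halve to 0.1 to 1.0 surfaces, or 4% to 40%.

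**The case against.** The main weakness is one cluster per arm per site, and the protocol discloses it. Matching would not cure it: even with half the block variance removed, the SD of the difference stays at 1.5 to 2.2 surfaces. That stands, and it limits what the fix can claim. It does not explain why the pairing rule is silent on likeness, since a similarity rule keeps the two-block layout and so respects the logistic constraint.

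Several stronger readings are tempting, and the documents do not support them:

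- **That distance is the only restriction on the blocks.** The setting already fixes peri-urban or rural class within each site.
- **That the protocol documents a tribal difference between the two Cuttack blocks.** Background contrasts Cuttack with Chandigarh, not one Cuttack block with the other. The AWC coverage norm, "each centre covering a population of 1000 in rural and urban areas and 700 in Tribal regions", is a national figure, and nothing says that any study AWC works under the lower one.
- **That tribal share is fully aliased with arm.** Tribal membership belongs to the child. With share gaps of 10 to 50 points both groups can occur in both blocks, so the imbalance is partial and can be adjusted for. It is block that is fully aliased.
- **That tribal membership will not be collected.** It is not named, but the confounder list is open-ended and Table 1 has a socio-demographics row at baseline. A condensed article may leave the item to the full protocol.

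The unit actually compared is also the cluster of neighbouring AWCs, so likeness of whole blocks is only a partial safeguard. This too is fair and is taken into the fix.

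**Conclusion.** The point holds in this form. Within a site, block is completely confounded with arm. Beyond the rural or peri-urban setting, the one stated rule for the pair is distance, and the named between-group tests carry no committed adjustment. Followed as written, the plan lets any block difference pass into the dmfs contrast.

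The aliasing is exact within a site and needs no assumption. The sizes do: the chance SD of 2.2 to 3.1 surfaces rests on an assumed block ICC of 0.01 to 0.02, and the Cuttack example of 0.2 to 2.0 surfaces (0.1 to 1.0 pooled) rests wholly on assumed gaps in composition and caries. They show that a modest difference between blocks could rival the planned 2.47. They do not show that such a difference exists. The change is worth making because it is cheap and a better rule, but it leaves the basic limit of the layout in place.

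**What to change.** 1. In Study design, add a second selection rule. Among block pairs at a site that meet the distance rule, choose before allocation the pair closest on available figures such as tribal share and children per AWC. Where possible, apply the same criterion to the AWC clusters within the pair, since these are what is compared. Then randomise within the pair. Rural or peri-urban class need not be a matching variable, because the setting already fixes it.

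2. Make sure that tribal membership of the child is recorded at enrolment. Adjust the Cuttack dmfs comparison for it, together with the socio-economic status and eating patterns already collected.

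3. State that matching and adjustment reduce the confounding of block with arm but cannot remove it: unmeasured and area-level differences remain.

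If the blocks are already fixed, the first change is no longer possible. The second still applies, and the statement in the third should then refer to adjustment alone.

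The cost is desk work before allocation, provided that block-level or AWC-level figures can be had (the article does not say), and at most one item on the enrolment form. The downside is fewer candidate pairs and possibly a shorter distance between the chosen blocks, to be weighed against contamination.
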